## Background

Across the developed and developing world the population is ageing. In Australia it is predicted that, compared to 2005 the proportion of the population over 65 years of age will increase from 13% to 24%, by 2036 [1]. With this increase, the demand on Emergency Department (ED) services by older persons living in the community or in residential aged care facilities (RACF) will increase [1–3]. A systematic review of 27 studies from around the world has demonstrated that the rate of transfer to EDs from RACFs is 0.1–1.5 transfers per RACF bed/year [4].

As a result of this ageing of the population it is imperative that the health care system develop safe models of care (MOC) that span both the community and hospital health care sectors. While the ED is uniquely designed to care for the critically ill or injured, it is often a suboptimal environment for the provision of care to the frail, older person [5, 6]. Prior research shows that older persons who develop an acute illness or who have an acute exacerbation of a chronic condition, have complex medical needs and the doctors and nurses who manage their initial care in the ED often have limited experience in geriatric medicine [7, 8]. Several studies have shown that this situation leads to: under-triage; higher rates of admission; delayed and fragmented care; longer stays in the ED; and unnecessary investigations and invasive interventions [9–19]. For patients from RACFs this is particularly true. During admission to hospital, patients from RACFs are at high risk of complications such as delirium, urosepsis, falls and death [20–22]. Patients from RACFs who develop an acute illness or an exacerbation of a chronic condition also suffer high rates of re-presentation to the ED and subsequent re-admission to hospital [2, 10, 12, 14].

Several studies indicate that a large percentage of frail older persons living in the community or RACFs express a preference for treatment in their home if appropriate [23, 24]. Despite this, approximately 60% of ED presentations lead to hospital admission [25, 26]. In an attempt to keep frail older persons at their place of residence during an acute illness, several MOC have been designed and tested. Broadly, the different MOC are divided into those that: i) provide in-home care or outreach of services from one service to another [12, 24, 27, 28]; ii) provide prioritisation or geriatric focused care in the ED [29–32]; or iii) support or enhance primary care [28, 33].

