### Setting

This study is set on the Sunshine Coast of Queensland, Australia. In Australia, the current percentage of people aged 65 years and over accounts for around 14% of the population [1]. On the Sunshine Coast this percentage is expected to increase to 17% by 2031 [36]. The study will be conducted in the Nambour General Hospital, situated in the Sunshine Coast and Hospital Health Service (SCHHS). Nambour General Hospital is one of four public hospitals in the SCHHS. NGH is the base hospital containing 373 beds and the three secondary hospitals have a combined total of approximately 531 beds. All four hospitals have an ED where both adults and children are treated. The study ED has an annual presentation of 52,410 patients; 18% of whom are over the age of 70 years [36]. Locating the research in the SCHHS will provide evidence of the effectiveness and feasibility of this MOC in a regional setting.

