#### Study 3: Health economics

Individual patient data will be collected from the Hospital Based Corporate Information System (HBCIS) for Nambour General Hospital. HBCIS is a patient record system for hospital administration that includes information such as patient details, ED presentation complaint, diagnosis, length of stay, bed and menu assignment, discharge status and costs associated with ED episode and inpatient episode of care (if the patient was admitted for inpatient care). For the economic analysis, data will be collected from the two periods in time pre and post GEDI MOC implementation. The historical data during the period of 1^st^ January 2012 – 31^st^ December 2012. The experimental data will be collected for the period of 1^st^ September 2015 to 31^st^ August 2016. While de-identified, the costing data contains sufficient information on hospital resource utilisation such as triage category, length of stay, and treatment received as well as discharge status.

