##### Data analysis

A multivariate cost function will be estimated to determine average cost per patient, for before- and after-GEDI MOC scenarios. The function takes into account important determinants of individual cost such as age, severity, length of stay and procedures received while in the ED. In the cost effectiveness analysis, we will estimate the average difference in number of admissions for the before- and after-GEDI scenarios. The number of avoidable admissions will be converted to cost savings using the results of the cost analysis above, and compared against the implementation cost for the GEDI MOC. If the cost savings is larger than the implementation cost, the GEDI MOC can be viewed as cost effective.

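### The Study 3 rule for calling GEDI cost effective tests cost saving only, states no uncertainty, and rests on a number of admissions with no denominator or time trend

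*Protocol article*

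**What the plan says.** The analysis section of Study 3 (Health economics) sets out a chain of steps. A multivariate cost function gives average cost per patient before and after GEDI: "The function takes into account important determinants of individual cost such as age, severity, length of stay and procedures received while in the ED". For cost effectiveness, "we will estimate the average difference in number of admissions for the before- and after-GEDI scenarios". Then "The number of avoidable admissions will be converted to cost savings using the results of the cost analysis above", and the result is set against implementation cost. The verdict follows: "If the cost savings is larger than the implementation cost, the GEDI MOC can be viewed as cost effective".

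The periods are fixed in the same study: "The historical data during the period of 1^st^ January 2012 – 31^st^ December 2012" and "The experimental data will be collected for the period of 1^st^ September 2015 to 31^st^ August 2016". The Background expects that "the demand on Emergency Department (ED) services by older persons living in the community or in residential aged care facilities (RACF) will increase".

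Confidence intervals and a linear date trend are specified, but in the analysis section of Study 1. Mortality and ED re-presentation at 72 hours and 28 days are Study 1 outcomes. None of these is carried into the Study 3 rule.

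**The concern.** The economic evaluation is one of three stated aims, and this one sentence decides what it will conclude. Three features of the rule are at issue.

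- **Construct.** Savings above the cost of the service show that it saves money. Cost effectiveness relates cost to health effect, and no effect on patients appears in the rule. This matters for a model meant in part to replace hospital admission, where fewer admissions could come with more returns or deaths.
- **Uncertainty.** The rule asks only whether one amount is larger than another.
- **Effect measure.** A number of admissions depends on how many people present as well as on the proportion admitted. GEDI is meant to change the proportion. The protocol itself expects the number presenting to rise.

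A manager reading the result could adopt or reject the service on a label that the analysis does not earn.

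**Working it through.** **Step 1: what the rule can and cannot say.** The protocol gives no cost, threshold or sample size for Study 3, so there is no figure to reproduce. The rule can be checked by its cases:

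| Savings vs GEDI cost | Mortality / re-presentation | Label under the rule |
|---|---|---|
| larger | better or unchanged | cost effective |
| larger | worse | cost effective |
| smaller | better | not cost effective |
| smaller | worse or unchanged | not cost effective |

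The label follows the first column only. Rows two and three are the errors, and they need no numerical assumption.

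**Step 2: inputs for the count.**
- Volume: "The study ED has an annual presentation of 52,410 patients; 18% of whom are over the age of 70 years" (Setting). 52,410 × 0.18 = 9,434. Taking this as the Time 1 volume is an assumption, and it covers everyone over 70, not only frail patients.
- Admission proportion: about 60%, a general figure from the Background and not site data. 9,434 × 0.60 = 5,660 admissions a year.
- Spacing: 1 January 2012 to 1 September 2015 is 3 years 8 months, or 3.67 years. Both periods have 366 days, so unequal length is not a problem.
- Growth g in presentations: not given, so it is assumed. The nearest figure is the Background's national share of people over 65, rising from 13% to 24% between 2005 and 2036: (24/13)^(1/31) − 1 = 2.0% a year. That is a population share, not local ED volume.

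**Step 3: raw count against rate.** Time 2 volume N2 = 9,434 × (1 + g)^3.67. Suppose the admission rate truly falls from 60% to 55% (an assumption).

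| g per year | N2 | Count change at unchanged 60% | Truly averted, N2 × 0.05 | Apparent fall, 5,660 − 0.55 × N2 |
|---|---|---|---|---|
| −2% | 8,760 | −404 | 438 | 842 |
| 0% | 9,434 | 0 | 472 | 472 |
| +1% | 9,784 | +210 | 489 | 279 |
| +2% | 10,144 | +426 | 507 | 81 |

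At 2% growth the count hides 426 of 507 averted admissions. At a 2% yearly decline it shows 404 fewer admissions even if GEDI changes nothing.

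The count shows no change when N2/9,434 = 0.60/0.55 = 1.091, which is growth of 1.091^(1/3.67) − 1 = 2.4% a year.

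**Step 4: chance variation.** With no growth and no effect, the standard error of the difference between two yearly counts is √(2 × 9,434 × 0.6 × 0.4) = 67 (binomial, volume fixed) to √(2 × 5,660) = 106 (Poisson). The 95% half-width is 1.96 × 67.3 = 132 to 1.96 × 106.4 = 209 admissions. A rule that compares point values takes no account of this.

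**The case against.** The best defence has four parts.

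- The wording is permissive, and the third research question asks only about costs. Admissions also fit GEDI's aim of preventing unnecessary ones. This softens the point, but the sentence still attaches the cost-effectiveness label.
- Mortality and re-presentation are reported in Study 1, so a reader would see any harm. True, but the rule does not make its label depend on them.
- A condensed article may leave intervals to a fuller document. This is fair for silence on method. Here, however, the decision rule is printed in full without an interval, so a later plan would have to change it.
- The words average and scenarios allow a per-patient or modelled quantity, and the aims speak of admission rates. This stands: the raw-count reading is likely, not certain. No denominator or trend is stated, and the listed covariates belong to the cost-per-patient function.

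Four stronger readings are tempting, and the documents do not support them.

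- *Chance alone meets the rule half the time.* This holds only when true savings exactly equal implementation cost.
- *Growth cancels or reverses the benefit.* At 2% a year a five-point fall still shows about 80 fewer admissions. Reversal needs faster growth or a smaller effect, and no growth rate is given.
- *The rule leans in GEDI's favour.* Growth in presentations biases the count against GEDI. Only falling volume, or an unrelated fall in admissions, favours it.
- *Savings are overpriced because averted admissions are the cheap ones.* Nothing in the documents shows this, and the cost function could give case-specific predictions.

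**Conclusion.** The point holds. Without any numerical assumption, the rule tests net cost saving and labels it cost effectiveness. It can give the wrong label in both directions, and it states no uncertainty.

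The effect-measure part depends on reading the number of admissions as a raw count. On that reading, a real five-point fall worth about 507 admissions shows as about 80 at 2% yearly growth, and a 2% yearly decline creates about 404 false ones. These sizes rest on 9,434 as the Time 1 volume, the general 60% admission figure, and assumed growth and effect. They show how sensitive the measure is and do not predict the result. If a per-patient or adjusted difference is meant, this part is resolved by saying so, and the other two remain.

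**What to change.** 1. Call the result of the present comparison cost saving. Use cost effective only when net cost is reported jointly with the Study 1 effects on mortality and 28-day re-presentation.
2. Define averted admissions as the adjusted difference in admission risk, with the same covariates and date trend as Study 1, multiplied by the number of Time 2 presentations.
3. Report net cost (GEDI cost minus savings) with a bootstrap 95% CI, and base the conclusion on that interval.

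The data are already to be collected, so the cost is revised wording and a bootstrap. The drawback is that the claim becomes harder to reach. The date trend adds to this: no data are taken between 1 January 2013 and 31 August 2015, so the trend must be learned within the two windows and the interval may be wide.

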##### Data analysis

Descriptive statistics will be used to describe the intervention and control groups including frequencies, percentages, appropriate measures of central tendency and distribution. We will use survival analysis to jointly model length of stay and disposition, with the four destinations as competing risks. We will use survival analysis for ED representations with out-of-hospital mortality as a competing risk. All models will adjust for the patient level factors of gender, age, triage score, season, day of the week and time of presentation. Pre-post designs are vulnerable to confounding by other changes over time that may be attributed to the intervention [39]. To control for this, we will include a linear trend (based on date) in all models to account for gradual changes that are not captured in the individual variables, e.g., experience of healthcare workforce. We will also adjust for season using a sinusoid with an annual cycle to control for the winter peak in morbidity [42]. The survival analyses will use Cox models and we will check the proportional hazards assumption. The models’ residuals will be checked for outliers and correlation over time. We will calculate Cook’s influential statistic and examine relatively large outliers. We will calculate the variance inflation factor and remove variables with a score above five on the basis that they are co-linear. The key outcome will be the mean effect of the intervention together with 95% confidence intervals. The results will be reported using the Strengthening the Reporting of Observational Studies in Epidemiology (STROBE) guidelines [43].

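### Study 3 calls GEDI cost effective when a point estimate of savings exceeds the implementation cost, with no account of sampling error

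*Protocol article*

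**What the plan says.** The Data analysis section of Study 3 builds the verdict in four steps.

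- Cost: "A multivariate cost function will be estimated to determine average cost per patient, for before- and after-GEDI MOC scenarios".
- Effect: "we will estimate the average difference in number of admissions for the before- and after-GEDI scenarios".
- Conversion to money: "The number of avoidable admissions will be converted to cost savings using the results of the cost analysis above".
- Verdict: "If the cost savings is larger than the implementation cost, the GEDI MOC can be viewed as cost effective".

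Neither that section nor the Study 3 introduction mentions a confidence interval, a bootstrap, a sensitivity analysis or a probability of cost effectiveness. The protocol's only commitment to intervals is in the Data analysis section of Study 1: "The key outcome will be the mean effect of the intervention together with 95% confidence intervals". Nothing links it to the Study 3 criterion.

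**The concern.** Both factors of the saving are estimates. The admission difference compares one 12-month period with another and varies by chance, and the cost comes from a fitted regression. The criterion treats their product as known and reads a verdict from which side of the implementation cost it falls on. A chance fall in admissions can therefore earn the label.

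The economic evaluation is one of the three study aims, and the abstract offers the results as guidance on costs for services considering the model. A reader deciding on funding would be told that GEDI is cost effective without learning whether the data separate that from no saving at all.

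**Working it through.** The protocol states no sample size, error rate or precision for Study 3, so there is no figure of its own to reproduce. The check asks how the stated rule behaves.

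**Inputs from the protocol**
- Presentations (Setting): "The study ED has an annual presentation of 52,410 patients; 18% of whom are over the age of 70 years". 52,410 × 0.18 = about 9,434 a year.
- Admission proportion (Background): "approximately 60% of ED presentations lead to hospital admission". This is a literature figure, used here as a planning value.
- Staffing (Intervention): 2.4 + 0.8 = 3.2 nursing FTE.
- Periods (Study 3): 12 months against 12 months.

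**Assumed, because the protocol gives no costs**
- AUD 100,000 to 150,000 per FTE and AUD 3,000 to 8,000 per admission.

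**Step 1: precision of the admission difference.**
SE of the difference in proportions = √(2 × 0.6 × 0.4 / 9,434) = 0.00713. In admissions: 0.00713 × 9,434 = 67.3 a year. 95% half-width: 1.96 × 67.3 = 132, or 1.4% of presentations. For admission proportions from 0.4 to 0.7 the SE stays between 63 and 69.

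**Step 2: break-even, B = implementation cost / cost per admission.**
Low: 3.2 × 100,000 / 8,000 = 40 admissions. High: 3.2 × 150,000 / 3,000 = 160 admissions.

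**Step 3: probability of the label when GEDI has no effect on admissions, 1 − Φ(B / SE).**

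| B (admissions a year) | B / 67.3 | Probability of label |
|---|---|---|
| 40 | 0.594 | 27.6% |
| 75 | 1.114 | 13% |
| 100 | 1.486 | 7% |
| 160 | 2.377 | 0.9% |

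The probability exceeds 2.5% whenever B is below about 132, and is about 0.15% at B = 200. A binomial simulation (400,000 runs) that added sampling error in the unit cost, with an assumed coefficient of variation of 2, gave almost the same results (13.2% at B = 75). The admission difference therefore dominates the uncertainty.

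**Step 4: sensitivity.**
- Only a quarter of the presentations analysed, as an illustration of a frail subgroup: SE = √(2 × 2,358.5 × 0.24) = 33.6. The probabilities become 1 − Φ(40/33.6) = 12% and 1 − Φ(160/33.6), effectively zero.
- Implementation cost doubled: B = 80 to 320, giving 1 − Φ(80/67.3) = 12% down to effectively zero.
- Repeat presentations doubling the variance: SE = 67.3 × √2 = 95.2, giving 1 − Φ(40/95.2) = 34% and 1 − Φ(160/95.2) = 5%.

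**Step 5: what the verdict hides.**
At B = 40, an estimate that just clears the bar carries a 95% interval of 40 ± 132, that is −92 to 172 avoided admissions. The rule reports it in the same words as a large and well-determined saving.

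**The case against.** Several points on the other side have force.

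- **Condensed article.** Interval methods for costs are often left to a full analysis plan, and the sentence is permissively worded. That excuses the absence of method detail. It does not excuse a criterion that is written out, and it is the only one given. Study 1's planned intervals cover models of disposition, which includes admission, so part of the uncertainty may be reported elsewhere. It still does not reach the verdict.
- **Size depends on unseen inputs.** This stands. Salaries and admission costs are assumed, and the implementation cost here counts nurses only, although the Intervention section also names a physician lead and education work. The denominator is everyone over 70, as in the Study aims, whereas the Samples section describes frail older persons. Each of these could lower the probability.
- **Expected-value decisions are legitimate.** This also stands. Adopting a service when its expected saving exceeds its cost is a recognised rule. Requiring the lower 95% limit of net saving to exceed zero is a different, contestable convention. The protocol is not wrong for lacking it.

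Two stronger readings are tempting.

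- A reader might infer that Study 1's linear date trend, which could inflate the variance of the period effect about 48-fold, raises the no-effect probability to 37% to 47%. The documents do not support this. The trend is specified for the Study 1 models, and Study 3 states none for the admissions comparison. Study 1 also removes variables with a variance inflation factor above five, so inflation on that scale would not survive the plan as written.
- A reader might infer a special failure from the fact that the rule passes GEDI half the time at exact break-even. Any roughly unbiased, symmetric point-estimate rule does so, and at that point either verdict costs nothing.

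**Conclusion.** The point holds in a limited form. The stated criterion is a bare comparison of point estimates, so chance alone can produce the label. With all presentations over 70, 60% admitted and independent presentations, the SE is about 67 admissions a year. The no-effect probability of the label is then about 1% to 28% for break-evens of 160 to 40 admissions.

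The SE rests on protocol figures; the break-evens rest on assumed costs. The probability could therefore be negligible or material, and the protocol does not allow one to say which. This is a weakness in how the conclusion is drawn, correctable before analysis. It is not evidence that the economic study will mislead.

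**What to change.** Replace the last sentence of the Study 3 Data analysis section with wording such as:

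*Net saving (saving minus implementation cost) will be estimated with a patient-level bootstrap that re-estimates the admission difference and the unit cost together in each resample. It will be reported with a 95% interval and the probability that it exceeds zero. The conclusion will be worded from these, and the result will be described as uncertain when the interval includes zero.*

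Resampling patients, with all their presentations, also allows for repeat attendance. No fixed lower-limit threshold is needed; decision makers can weigh the probability themselves. The interval covers sampling error only. It does not cover bias from other changes between 2012 and 2015–16, and the report should say so.

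The cost is modest. Patient-level cost and admission data are already to be collected, so the change means some extra analysis and a less clear-cut verdict.

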## Discussion

GEDI is an innovative MOC that provides a single point of contact in the ED for RACF staff, primary health services and secondary health services. The primary focus is to deliver high quality care for frail older persons living in the community or RACF through seamless continuity of care as they transition through the ED. Secondly, the GEDI MOC aims to facilitate community care strategies and thus acts as a hospital substitution model.

Complex, multifocal interventions, such as the GEDI MOC, are frequently implemented without rigorous evaluative research. This study will provide not only a description of the structures and processes required for successful implementation of the MOC but will also provide older person and cost related outcomes.

